### 9.3.5.2 Severity of Solicited Systemic Adverse Events

The subject or legal representative will determine the severity of solicited systemic AEs (fever, malaise, headache, rash, and myalgia) according to the criteria in [Table 9.3-2](#)~~Table 9.3-2~~[Table 9.3-2](#). For fever, the severity will be determined according to the criteria in [Table 9.3-2](#)~~Table 9.3-2~~[Table 9.3-2](#), based on the information in the electronic diary recorded by the subject or legal representative. The investigator or subinvestigator will determine the severity of serious solicited systemic AEs and solicited systemic AEs leading to permanent discontinuation of study treatment or withdrawal from the study according to the criteria in [Table 9.3-2](#)~~Table 9.3-2~~[Table 9.3-2](#), with reference to the information recorded in the electronic diary by the subject or legal representative.

Table 9.3-2 Severity of Solicited Systemic Adverse Events

| AE       | Mild
(Grade 1)                                     | Moderate
(Grade 2)                                                                                    | Severe
(Grade 3)                                                                               |
|----------|-------------------------------------------------------|----------------------------------------------------------------------------------------------------------|---------------------------------------------------------------------------------------------------|
| Fever    | 37.5°C–38.4°C                                         | 38.5°C–38.9°C                                                                                            | 39.0°C –                                                                                          |
| Malaise  | Tolerable with no interference with daily activities. | Some interference with daily activities.                                                                 | Significantly prevents daily activities, such as school life.                                     |
| Headache | Tolerable with no interference with daily activities. | Repeated use of anti-inflammatory analgesics for > 24 hours, or some interference with daily activities. | Not alleviated by the repeated use of anti-inflammatory analgesics, or prevents daily activities. |
| Rash     | Local (non-injection sites).                          | Systemic.                                                                                                | Systemic rash, accompanied by symptoms such as pain, blisters, and ulcers.                        |
| Myalgia  | Tolerable with no interference with daily activities. | Some interference with daily activities.                                                                 | Significantly prevents daily activities, such as school life.                                     |

### 9.3.5.3 Severity of Unsolicited Adverse Events

The investigator or subinvestigator will determine the severity of "tenderness of injection site," among the unsolicited injection site AEs confirmed by medical interview, telephone contact, etc.,

Confidential

according to the criteria in [Table 9.3-3](#)~~Table 9.3-3~~[Table 9.3-3](#).

Table 9.3-3 Severity of Unsolicited Adverse Events at the Injection Site (Tenderness)

| AE                           | Mild
(Grade 1)                               | Moderate
(Grade 2)                         | Severe
(Grade 3)             |
|------------------------------|-------------------------------------------------|-----------------------------------------------|---------------------------------|
| Tenderness of injection site | Mild discomfort to touch at the injection site. | Discomfort with movement of the injected arm. | Significant discomfort at rest. |

The investigator or subinvestigator will determine the severity of "nausea," "vomiting," and "diarrhea," among the unsolicited systemic AEs confirmed by medical interview, telephone contact, etc., according to the criteria in [Table 9.3-4](#)~~Table 9.3-4~~[Table 9.3-4](#).

Table 9.3-4 Severity of Unsolicited Systemic Adverse Events (Nausea, Vomiting, Diarrhea)

| AE       | Mild
(Grade 1)                                                                                                            | Moderate
(Grade 2)                         | Severe
(Grade 3)                                                                                       |
|----------|------------------------------------------------------------------------------------------------------------------------------|-----------------------------------------------|-----------------------------------------------------------------------------------------------------------|
| Nausea   | Tolerable with no interference with daily activities.                                                                        | Some interference with daily activities.      | Requires medication.                                                                                      |
| Vomiting | 1 to 2 episodes per 24 hours.                                                                                                | ≥ 3 episodes over 24 hours.                   | Requires outpatient intravenous drip infusion (hydration).                                                |
| Diarrhea | Is tolerable with no interference with daily activities, or is associated with 2 to 3 episodes of loose stools per 24 hours. | 4 to 5 episodes of loose stools per 24 hours. | ≥ 6 episodes of watery stools per 24 hours, or requires outpatient intravenous drip infusion (hydration). |

The investigator or subinvestigator will determine the severity of unsolicited AEs other than "tenderness of injection site," "nausea," "vomiting," and "diarrhea" confirmed by medical interview, telephone contact, etc., according to the following criteria:

- Mild: Awareness of sign or symptom, but easily tolerated, i.e., does not interfere with subject's usual function.
- Moderate: Interfering with daily activities.
- Severe: Incapacitating with inability to work or do usual activity, i.e., interferes significantly with subject's usual function.

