## 9.3 Adverse Event

### 9.3.1 Definition of Adverse Event

An AE is any untoward medical occurrence in a subject administered an investigational product and that does not necessarily have to have causality with the treatment. An AE can therefore be any unfavorable and unintended sign (eg, an abnormal clinical laboratory finding), symptom, or disease temporally associated with the use of an investigational product, whether or not considered related to the investigational product.

The AEs in this study that are specified in Section 9.3.3 and Section 9.3.4 will be referred to as

Confidential

"solicited AEs" and "unsolicited AEs," respectively. The investigator or subinvestigator will be responsible for determining the occurrence of nonserious unsolicited AEs, SAEs, and AEs leading to permanent discontinuation of study treatment or withdrawal from the study, including clinical laboratory evaluations. The presence or absence of nonserious solicited AEs will be determined and spontaneously reported by the legal representative using the electronic diary.

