### 9.3.4 Unsolicited Adverse Events

Unsolicited AEs are defined as AEs other than "solicited AEs."

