### 9.3.5 Severity Evaluation

The subject or legal representative will evaluate the severity of solicited systemic AEs (injection site and systemic) according to the definitions in Section 9.3.5.1 "Severity of Solicited Injection Site Adverse Events" and Section 9.3.5.2 "Severity of Solicited Systemic Adverse Events," and record the evaluation in the electronic diary.

The investigator or subinvestigator will evaluate the severity of nonserious unsolicited AEs, SAEs, and AEs leading to permanent discontinuation of study treatment or withdrawal from the study according to the definitions in Section 9.3.5.1 "Severity of Solicited Injection Site Adverse Events," Section 9.3.5.2 "Severity of Solicited Systemic Adverse Events," and Section 9.3.5.3 "Severity of Unsolicited Adverse Events."

Difference between severity and seriousness: Severity is used to describe the intensity of a specific event while the event itself may be of relatively minor medical significance (eg, severe headache). This is not the same as "seriousness," which is based on patient/event outcome at the time of the event.

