### 9.4.1 Combined Elevations of Aminotransferases and Bilirubin

Combined elevations of aminotransferases and bilirubin, either serious or nonserious and whether or not causally related, as a potential case of Hy's Law (alanine aminotransferase [ALT] or aspartate aminotransferase [AST]  $\geq 3 \times$  upper limit of normal [ULN] and blood bilirubin  $\geq 2 \times$  ULN, with no increase in alkaline phosphatase (ALP), in the absence of other factors for the increases in both aminotransferases and total bilirubin), even when evaluated to be due to disease progression by the investigator or subinvestigator, should always be reported to the sponsor using the eCRF, with the investigator's or subinvestigator's evaluation of seriousness, causality, and a detailed narrative. This event should be reported within 24 hours of the investigator's or subinvestigator's awareness of the event.

If study drug administration is permanently discontinued due to liver enzyme abnormalities, the subject will be followed as described in Section 5.8 until the AE recovers or resolves to the condition

Confidential

before the occurrence of the AE and disappears, AE is recovering or resolving, or AE is stabilized in order to determine the nature and severity of the potential liver injury.

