#### 9.6 Reporting of Serious Adverse Events: Procedures for the Investigator or Subinvestigator

The types of events listed below should be reported by the investigator or subinvestigator to the sponsor using the EDC, promptly after becoming aware of relevant information (within 24 hours of awareness).

The investigator should also report the detail of the event in writing promptly to the sponsor and the head of the study site. The written report to the head of the study site should be made in accordance with the procedures and format specified by the study site.

- SAEs (See Section 9.3.2 for definitions.)
- Combined elevations of aminotransferases and bilirubin, either serious or nonserious, as a potential case of Hy's Law (See Section 9.4.1 for details.)

All events (serious and nonserious) that fall under either of the above categories should be reported with the investigator's or subinvestigator's evaluation of the seriousness, severity, and causality with the study drug. A detailed narrative that summarizes the course of the event, including its evaluation, treatment, and outcome, should also be submitted. Specific or estimated dates of event onset, treatment, and resolution should be included when available. Medical history, concomitant medications, and clinical laboratory data that are relevant to the event should also be summarized in the narrative. For fatal events, the narrative should state whether an autopsy was or will be performed, and include the results if available. Source documents (including medical reports) will be retained at the study site and need not be submitted to the sponsor for the purpose of SAE reporting.

Upon receipt of urgent safety queries from the sponsor, the investigator or subinvestigator must follow and address them promptly. Follow-up information and responses to non-urgent safety queries

Confidential

should be combined for reporting to provide the most complete data possible in the eCRF.

In situations where EDC is not available, the paper serious adverse event report (SAVER) form should be completed and faxed or emailed along with the fax transmission form provided to the sponsor clinical safety and pharmacovigilance (CSPV) department. The SAVER form should be completed as soon as possible after EDC is available. For additional instructions, refer to the CRF Completion Guidelines (CCG).

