##### 11.4.5.1.2 Analysis of Unsolicited Adverse Events

The number and proportion of subjects with unsolicited TEAEs that are reported within 28 days after study drug administration will be calculated by system organ class (SOC), by preferred term (PT), and by administration arm. In addition, unsolicited TEAEs will be summarized according to their severity and causality with the study drug. Similarly, the number and proportion of subjects with TEAEs leading to permanent discontinuation of study treatment or withdrawal from the study will be summarized in a table. Adverse reactions will be tabulated in a similar manner.

Confidential

A listing for unsolicited AEs (including TEAEs), including the verbatim term, PT, SOC, severity, and causality with the study drug, will be prepared for each subject. Any other required data should be included in the listing.

Subgroup analyses will be performed on the frequency of unsolicited AEs according to baseline characteristics (eg, sex, history of SARS-CoV-2 infection, vaccination with SARS-CoV-2 vaccine). Similar subgroup analyses will also be performed for adverse reactions.

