#### 11.4.5.2 Analysis of Clinical Laboratory Data

For hematology and blood chemistry test data (quantitative values), summary statistics of the measurement and the change from baseline at each time point will be calculated, and the time course of the measurements will be graphically represented.

For urinalysis data (qualitative values), a shift table of the baseline and post-treatment value at each time point will be prepared.

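### Section 9.3.5.3 grades residual unsolicited AEs by loss of function only, so an AE that is purely a laboratory finding in a symptom-free subject can be graded at most Mild

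*Protocol*

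**What the plan says.** Section 9.3.1 counts as an AE "any unfavorable and unintended sign (eg, an abnormal clinical laboratory finding), symptom, or disease temporally associated with the use of an investigational product". Section 9.3.4 makes everything outside the solicited terms unsolicited ("Unsolicited AEs are defined as AEs other than" the solicited ones). Section 9.3.5 places the grading duty at the site: "The investigator or subinvestigator will evaluate the severity of nonserious unsolicited AEs, SAEs, and AEs leading to permanent discontinuation of study treatment", or to withdrawal from the study, using Sections 9.3.5.1 to 9.3.5.3.

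Section 9.3.5.3 has specific criteria for tenderness, nausea, vomiting and diarrhea. All other unsolicited AEs go to a three-step scale that starts with "Mild: Awareness of sign or symptom, but easily tolerated, i.e., does not interfere with subject's usual function". Moderate requires that daily activities are disturbed. Severe requires incapacity or marked loss of usual function.

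Section 9.4.1 requires combined aminotransferase and bilirubin elevations to be reported, "either serious or nonserious and whether or not causally related, as a potential case of Hy's Law", within 24 hours of awareness. Section 9.6 asks that they come with the "investigator's or subinvestigator's evaluation of the seriousness, severity, and causality with the study drug".

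In the analysis, Section 11.4.5.1.2 states that "unsolicited TEAEs will be summarized according to their severity and causality with the study drug". For hematology and chemistry, Section 11.4.5.2 states that "summary statistics of the measurement and the change from baseline at each time point will be calculated", together with time-course graphs. Section 11.1 sets the default for continuous variables as number of subjects, mean, standard deviation, minimum, median and maximum.

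**The concern.** A functional scale suits symptoms. A laboratory abnormality often produces neither awareness nor loss of function, so the scale has nothing to measure and returns its lowest step however large the deviation. The investigator must still enter a grade, and that grade feeds a planned safety table. What is at stake is whether the severity column for laboratory AEs carries information: a trivial and a marked finding in two subjects who both feel well would receive the same grade.

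The grade is assigned by the investigator during the study under a rule fixed in the protocol. The SAP can add displays of the raw values, but it does not set the rule under which sites enter severity.

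**Working it through.** No arithmetic applies: the protocol states no figure on this point and none is needed. The check follows one event through the text, then looks for any provision that would catch it elsewhere.

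1. **Can a laboratory finding be an AE?** Yes. Section 9.3.1 uses one as its example.
2. **Which class does it fall in?** Unsolicited. The solicited terms in Sections 9.3.3.1 and 9.3.3.2 are redness, swelling, induration, pain, warmth, pruritus, fever, malaise, headache, rash and myalgia.
3. **Must it be graded?** Yes, under Section 9.3.5, whether nonserious, serious or leading to discontinuation or withdrawal.
4. **Which scale applies?** Tables 9.3-1 and 9.3-2 cover the solicited terms. Tables 9.3-3 and 9.3-4 add tenderness, nausea, vomiting and diarrhea. None has a laboratory item. The cited toxicity grading guidance (reference 32) is attached only to these four tables. That leaves the residual scale.
5. **What grade results?** Without symptoms or functional interference, neither Moderate nor Severe can be met. Mild is the highest grade available for any value of ALT, AST, bilirubin, CK or platelets.

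The protocol's own special-interest event is the clearest test case. Section 9.4.1 defines it by ALT or AST at least 3 x ULN with bilirubin at least 2 x ULN, no rise in ALP and no other explanation. It has no symptom requirement. Section 9.6 requires a severity, and in a subject who feels well step 5 gives Mild. If the event is a TEAE (Section 11.4.5.1: onset or worsening up to 28 days after dosing), it enters the table of Section 11.4.5.1.2 at that grade.

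**How many laboratory findings get this far?** Section 9.2 governs isolated abnormalities. It lists four conditions for reporting them as AEs: symptoms, permanent discontinuation of study treatment, need for symptomatic treatment, and the investigator's clinical judgment. The list is joined by 'and'.

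- Read literally, all four must hold. Almost no symptom-free laboratory value then becomes an AE by this route. What remains is potential Hy's Law cases (reportable under Sections 9.4.1 and 9.6 regardless) and laboratory-based SAEs.
- Read as 'or', findings reported on clinical judgment alone are added.

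**Does another display show the size of the abnormality?** In part. Sections 11.1 and 11.4.5.2 together give the minimum and maximum of each measurement and of its change from baseline. No count of subjects by size of abnormality is named for hematology or chemistry, but such a count is SAP-level detail and its absence here is not an error.

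**The case against.** The strongest case on the other side has five parts.

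- **Section 9.2 keeps most symptom-free laboratory values off the AE page.** This stands, and it limits the point to the event types listed above. A reader might infer from Section 9.3.1 alone that every laboratory abnormality is misgraded; Section 9.2 does not support that. Counting all scheduled laboratory results would not measure the problem either, since nearly all of them need no grade.
- **Severity is separate from seriousness.** This stands. Section 9.3.5 says so. The 24-hour report and narrative for a potential Hy's Law case are triggered by the laboratory values. A reader might infer that a Mild grade lets such a case escape expedited reporting, or that Mild plus mandatory reporting is a contradiction. Neither follows.
- **Extreme values are visible elsewhere.** This stands. Minimum and maximum are default summaries, time courses are plotted, and unsolicited AEs are listed per subject with verbatim term and severity. A reader might infer that marked abnormalities, or a difference between arms, would be hidden altogether. They would not: extra laboratory AEs in one arm would still raise the counts by preferred term. Only the severity breakdown is uninformative.
- **AEs are to be reported as a diagnosis where one is available.** This does not help. The diagnosis, unless it is one of the four named events, is graded on the same functional scale.
- **The residual scale speaks of events established by interview, telephone contact and similar means, so laboratory AEs may lie outside it.** On that reading they have no severity scale at all, while Sections 9.3.5 and 9.6 still demand a grade. The gap changes form but remains.

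**Conclusion.** The point holds in a limited form. For AEs that are purely laboratory findings in symptom-free subjects, the stated rule permits no grade above Mild, including for a potential Hy's Law case that must carry a severity. The consequence is understated severity in the unsolicited TEAE table. Expedited reporting, narratives, the minimum and maximum laboratory values, and the primary, key secondary and solicited-AE results are unaffected.

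The protocol gives no expected number of laboratory AEs, so the size cannot be stated as a count. It could be zero if Section 9.2 is read literally and no potential Hy's Law case or laboratory-based SAE occurs. It would be larger if clinical judgment alone suffices for reporting. The conclusion assumes that investigators apply Section 9.3.5.3 as written and, for the table, that the event meets the TEAE definition. The change is worth making because it is cheap and replaces a rule that yields uninformative grades.

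**What to change.** Add to Section 9.3.5.3 that AEs which are laboratory findings are graded by the measured value on a published scale, chosen by the sponsor and fixed before unblinding. Keep the functional scale for all other unsolicited AEs outside the four named terms. In the same amendment, reconcile Section 9.2 with this rule by stating whether its conditions for reporting isolated laboratory abnormalities must all be met or whether any one suffices.

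Optionally, the SAP can add a count by arm of subjects in each laboratory grade. This is a useful extra and the point does not depend on it.

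The cost is one sentence in Section 9.3.5.3 and a clarified list in Section 9.2. The laboratory data are already collected at Day 1 and Day 29. Any laboratory AEs already graded at sites would need their grade revisited against the recorded values. The small downside is that some laboratory AEs will carry a higher grade than under the functional scale.

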### 9.3.6 Causality Evaluation

Solicited AEs (injection site and systemic), except for serious solicited AEs (injection site and systemic) and solicited AEs leading to permanent discontinuation of study treatment or withdrawal from the study, should be evaluated as "related" to the study drug.

The investigator or subinvestigator will evaluate the causality with the study drug for all nonserious unsolicited AEs, SAEs, and AEs leading to permanent discontinuation of study treatment or withdrawal from the study according to his/her own clinical judgment and the definitions below.

Confidential

The causality evaluation must be made based on the available information and can be updated as new information becomes available.

- Related:
  - The event follows a reasonable temporal sequence from study drug administration, and cannot be reasonably explained by the subject's clinical state or other factors (eg, disease under study, concurrent diseases, concomitant medications other than the study drug).
  - OR
  - The occurrence of event follows a reasonable temporal sequence from study drug administration, and is a known reaction to the drug under study or its chemical group, or is predicted by known pharmacology.
- Not related:
  - The event does not follow a reasonable temporal sequence from study drug administration or can be reasonably explained by the subject's clinical state or other factors (eg, disease under study, concurrent diseases, concomitant medications).

AEs evaluated as "related" to the study drug will be handled as adverse reactions.

